## Background

Emergence delirium (ED) is described as a “mental disturbance during recovery from general anesthesia consisting of hallucinations, delusions and confusion manifested by moaning, restlessness, involuntary physical activity, and thrashing about in bed” [1]. It can cause self-injury, dressing disruptions, surgical dehiscence, and dislodged indwelling catheters and can lead to parents’ and surgeons’ dissatisfaction with the anesthetic. The incidence of ED in pediatric patients after general anesthesia is reported to be between 10 and 80% [2]. Several factors, such as sevoflurane or desflurane anesthesia, younger age, pain, anxiety and the temperament of the child have been suggested to contribute to ED, but the precise etiology remains uncertain [2, 3]. Various studies have tried to reduce emergence delirium after anesthesia [4–6], but none have been completely effective.

Mothers usually spend a large amount of time with their children. Therefore, mothers can be assumed to contribute to their children’s emotional status and neurological development. In a previous study, maternal voice had special importance and enhanced involuntary attention [7]. Moreover, a mother’s voice elicited stronger activations in specific cerebral regions than an unknown voice in another study [8]. A recorded mother’s voice increased the activation of the prefrontal cortex compared to a stranger’s voice [9]. As shown by these studies, a mother’s voice has been shown to have a strong impact on both behavioral and neuronal responses in children.

However, the influence of a familiar voice, especially a mother’s voice, on a child during anesthetic emergence has been scarcely explored previously. Therefore, we will investigate whether maternal voice supports emotional stability and facilitates emergence during the emergence period. We hypothesized that children would show reduced ED and faster emergence when they heard their mothers’ recorded voices compared to a stranger’s recorded voice.

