### Intervention

At the preoperative waiting room, patients are premedicated with atropine (0.02 mg/kg) and ketamine (1 mg/kg) administered intravenously in the parental presence. After a patient enters the operating room, standard monitoring (electrocardiography, noninvasive arterial blood pressure, and pulse oximetry) and the Bispectral Index (BIS; VISTATM monitoring system; Aspect Medical Systems Inc., Norwood, MA, USA) will be applied. Anesthesia will be induced using fentanyl (1 mcg/kg) and 5–6% of sevoflurane via a scented facial mask. Rocuronium 0.6–0.8 mg/kg will be given to facilitate intubation. Anesthesia will be maintained with 1.5–2.0 MAC of sevoflurane and 50% oxygen, with a BIS target range of 40–60. At the end of the operation, pyridostigmine and glycopyrrolate will be administered to antagonize neuromuscular blockade. All patients will be given prophylactic antiemetics with dexamethasone 0.1 mg/kg and ondansetron 0.1 mg/kg.

According to the pre-assigned allocation, the patients will be stimulated to wake up by a repeated recording of the mother’s voice (maternal group) or a stranger’s voice (stranger group) at the end of the operation. The voice recording will be performed before the operation. In a calm environment, the mother or a woman who does not know the child is asked to speak the following sentences in her usual tone of voice:“OO (first name of child), wake up. Let’s go home with mommy. OO, wake up. Open your eyes. Take a deep breath.”

Only light patting on the shoulder and the recorded voice will be allowed to stimulate the patients. The recorded voice will be delivered to the patient repeatedly via noise cancelling headphones until extubation. An investigator who is blinded to the assigned intervention (EK) will check the BIS value and the end-tidal sevoflurane concentration (ET_sevo_ %) at the end of surgery, the extubation time, the eye opening or purposeful movement time and the time to BIS values of > 60, 70, and 80 during the emergence period. The BIS value will be included if the electromyography score is < 50% and the Signal Quality Index is > 75%. After gentle suctioning of oral secretions from the oropharynx, extubation will be carefully performed when the participants are able to achieve spontaneous breathing and obey verbal commands. Voice stimulation via headphones will be maintained until the patients arrive at the post-anesthesia care unit (PACU).

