### Measurements

The primary outcome measurement is the initial PAED score in the PACU. The secondary outcomes are hemodynamic parameters (heart rate, mean blood pressure), the duration of time from the cessation of anesthetics to a BIS score of 60/70 and 80 (BIS > –60/70/80 time), the eye-opening or purposeful movement time, the extubation time, the total consumption of analgesics, PACU stay time, and PAED, Watcha, and FLACC scores in the PACU.

The Modified Yale Preoperative Anxiety Scale (m-YPAS) will be used when the patients arrive at the preoperative waiting room with their parents before premedication [10, 11]. At the end of surgery, all anesthetics will be stopped immediately and the BIS value and the end-tidal sevoflurane concentration (ET_sevo_ %) are recorded. Hemodynamic parameters, including heart rate (HR) and mean blood pressure (MBP), will be checked at five time points; at the time of the cessation of anesthetics (baseline, t_0_), time to reach a BIS value of 60 (t_1_), time of extubation (t_2_), time of PACU arrival (t_3_), and time of PACU discharge (t_4_). BIS > 60, 70, and 80 times, defined as the time intervals from the cessation of anesthetics until the BIS reached values of 60, 70, and 80, respectively, will be measured. Eye-opening or purposeful movement time is defined as the interval from the cessation of anesthetics to-eye opening or purposeful movement of the patient. Extubation time, defined as the interval from the cessation of anesthetics until extubation, will also be measured.

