Upon arrival to the PACU, a blinded investigator will measure emergence delirium and pain scores at every 10 min for the first 30 min. Emergence delirium will be measured by two methods, the Pediatric Assessment of Emergence Delirium (PAED) and the Watcha scales. The PAED scale has five categories (eye contact, actions, awareness, restlessness, and consolability) scored from 0 to 4 and summed to obtain a total score with a range of 0–20 [12]. The degree of emergence delirium increased directly with the total scores. The Watcha scale is a four-point scale as follows [13]: 1, calm; 2, crying but can be consoled; 3, crying and cannot be consoled; 4, agitated and thrashing around. A total PAED score > 12 or a Watcha score > 2 at any time is considered post-anesthetic ED. Pain will be measured by Face, Legs, Activity, Cry and Consolability (FLACC) scores ranging from 0 to 15 [14]. In patients with a total PAED score > 12, a Watcha score > 2 or a FLACC score > 4 in the PACU, fentanyl 0.5 mcg/kg will be administered as a rescue medication and repeated if the agitation does not subside. Adverse events, such as postoperative nausea and vomiting, excessive secretions, laryngospasm, or desaturation and the total consumption of analgesics, will also be measured. The patients will be discharged when they are calm and meet a modified Aldrete score ≥ 9 [15], and the duration of the PACU stay will be recorded as the PACU stay time. The subjective satisfaction of the primary care giver such as a parent or the PACU nurse will be measured just before PACU discharge on a five-point scale as follows: 1, very disappointed; 2, disappointed; 3, so-so; 4, satisfactory; 5, very pleased.

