### Sample size

The primary outcome is the initial PAED score. In our pilot study, the mean difference of the PAED score between the stranger group and the maternal group was 1.6 with a standard deviation (SD) of 2.19. To attain an alpha value of 0.05 and a test power of 0.8, 30 patients are needed in each group using the following formula [16]. We plan to enroll a total of 66 patients to allow for a 10% dropout rate:$$ n\kern0.5em =\kern0.5em \frac{2{\left({z}_{a/2}+{z}_{\beta}\right)}^2\kern0.5em \cdotp \kern0.5em {\sigma}^2}{{\left({\mu}_c-{\mu}_t\right)}^2} $$

To compensate for the possibility of an over-estimated effect size of the pilot study, we will perform an interim analysis at 50% enrollment. If the sample size has significantly lower power than our expectation, we will recruit more patients. Otherwise, we will continue the study according to our initial sample size calculation.

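### The primary PAED score on PACU arrival carries no wakefulness condition, so a positive result could reflect faster arousal and not less delirium

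*Protocol article*

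**What the plan says.** All references are to the Protocol article.

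- **Primary outcome (Measurements).** "The primary outcome measurement is the initial PAED score in the PACU".
- **Timing (Measurements).** "Upon arrival to the PACU, a blinded investigator will measure emergence delirium and pain scores at every 10 min for the first 30 min". The legend of Fig. 1 lists PACU arrival as a time point. No level of arousal is required for the first score.
- **Scale (Measurements).** "The PAED scale has five categories (eye contact, actions, awareness, restlessness, and consolability) scored from 0 to 4 and summed", giving 0–20. On direction: "The degree of emergence delirium increased directly with the total scores". The wording of the item levels is not printed.
- **Binary definition of delirium (Measurements).** "A total PAED score > 12 or a Watcha score > 2 at any time is considered post-anesthetic ED".
- **Hypotheses (Background).** "We hypothesized that children would show reduced ED and faster emergence when they heard their mothers’ recorded voices". Less delirium and quicker waking are two separate expected effects.
- **State at extubation (Intervention).** "extubation will be carefully performed when the participants are able to achieve spontaneous breathing and obey verbal commands". One sentence in this section has the voice running until extubation and a later one until PACU arrival.
- **Planning values (Sample size).** "the mean difference of the PAED score between the stranger group and the maternal group was 1.6 with a standard deviation (SD) of 2.19", with 30 per group.
- **Test (Statistical analysis).** An unadjusted independent t test or Mann-Whitney U test on the initial score.

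**The concern.** The total rises with delirium, so eye contact, actions and awareness can only contribute by scoring how far they are absent. A child who is merely drowsy can lose points on all three without being agitated.

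The score is taken at a fixed event, and the intervention is a recording that urges the child to wake and is expected to speed waking. If the maternal arm is on average more alert at PACU arrival, its mean PAED can be lower even when restlessness and consolability are the same in both arms.

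The planned test cannot tell these explanations apart, and no listed outcome fills the gap. The BIS, eye-opening and extubation times all run from the cessation of anesthetics and do not describe the child when the first PAED is scored. Watcha is scored at the same visits, but its lowest grade (calm) does not distinguish a calm awake child from a sleeping one.

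What is at stake is the Discussion's intended conclusion, a new prophylactic option against emergence delirium. Quicker waking is a different claim.

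**Working it through.** **1. The plan's own figure.** Inputs from Sample size: difference 1.6, SD 2.19, alpha 0.05 (two-sided, from Statistical analysis), power 0.80.

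n = 2 × (1.960 + 0.842)² × 2.19² / 1.6² = 2 × 7.849 × 4.796 / 2.56 = 29.4, so 30 per group. The stated number is reproduced. By the noncentral t distribution, power at 30 per group is 0.795.

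**2. How much the three contact items can contribute.** With each item at level k, and restlessness and consolability at 0, the total is 3k: 3, 6, 9 or 12 for k = 1 to 4. Twelve is the ceiling, reached only with all three items at maximum. It does not satisfy > 12, and a quiet child is Watcha 1.

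**3. The target in item steps.** 1.6 / 3 = 0.53 of a step on each item.

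**4. A modest, uniform shift in alertness (assumed).** Suppose one arm is on average a fixed fraction of a step less alert on each of the three items, with no difference in restlessness or consolability. SD 2.19, 30 per group, two-sided t test at 0.05:

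| Shift per item | Mean difference | Chance of P < 0.05 |
|---|---|---|
| 0.25 step | 3 × 0.25 = 0.75 | 26% |
| 0.50 step | 3 × 0.50 = 1.50 | 74% |

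A uniform shift adds nothing to the within-arm SD, so the pilot SD cannot rule it out.

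**5. A subgroup of drowsy children (assumed).** If a drowsy child scores e points more than the others, the gap between arms in the drowsy share that alone yields 1.6 points is 1.6 / e. The least within-arm variance compatible with that gap g arises with a share of 0 in one arm and g in the other. Averaged over the arms it is e² × g × (1 − g) / 2. The pilot variance is 2.19² = 4.80.

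| Excess e | Gap g = 1.6 / e | Children of 33 | Least mean variance | Within 4.80? |
|---|---|---|---|---|
| 3 | 53.3% | 17.6 | 9 × 0.533 × 0.467 / 2 = 1.12 | yes |
| 6 | 26.7% | 8.8 | 36 × 0.267 × 0.733 / 2 = 3.52 | yes |
| 9 | 17.8% | 5.9 | 81 × 0.178 × 0.822 / 2 = 5.92 | no |
| 12 | 13.3% | 4.4 | 144 × 0.133 × 0.867 / 2 = 8.32 | no |

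**6. Large clusters at 12.** With 30% of children at 12 and the rest averaging 3, 5 or 7 (assumed; the article gives no mean), the mixture alone has variance 0.3 × 0.7 × (12 − mean)² = 17.0, 10.3 or 5.3. All exceed 4.80. With all other children at 0, an SD of 2.19 allows only about 3% of children at 12.

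Steps 5 and 6 assume that the pilot score was taken in the same way and that 2.19 is the within-group SD, as the formula uses it.

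**The case against.** A reader might infer that a drowsy child typically scores about 12, that drowsiness is counted as delirium, and that the false-positive risk or loss of power can be quantified. The documents do not support this.

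- **Twelve is a ceiling.** The item levels are not printed, and the stated direction shows only that poorer contact scores higher. Items at levels 1 to 3 give 3 to 9.
- **Full unresponsiveness is not the expected state.** Extubation requires obeying verbal commands, and one statement keeps the voice running until PACU arrival. A child may drift off in between, but no share is given.
- **The binary rule is not triggered.** A quiet child at 12 with Watcha 1 is not classed as having emergence delirium. A child with good contact who is agitated and inconsolable is caught by Watcha > 2.
- **Contact items belong to delirium.** The Background definition includes confusion as well as restlessness and thrashing, so scoring awareness is not in itself a fault.
- **The pilot SD argues against large clusters.** If the pilot score was taken in the same way, drowsiness is already in the 2.19, and adding it again to derive a power loss counts it twice.

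All of this stands, and it limits the point to the continuous score. It does not remove it. The primary test uses that score, modest shifts in alertness fit the pilot SD, and the outcome definition is fixed in the article itself. The existing arousal times and Watcha do not measure wakefulness when the score is taken.

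A further fair objection concerns making the first-awake score primary. Its timing would depend on a post-randomisation event that the intervention may change, it has no pilot SD, and recruitment is under way. That is a reason to use it only as a supporting analysis.

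**Conclusion.** The point holds for the interpretation of the continuous primary score. The first PAED score has no stated wakefulness condition, up to 12 of its 20 points can come from reduced arousal, and the intervention is itself expected to speed arousal. A positive primary result could therefore arise from faster waking without less delirium.

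The size of this effect in the trial cannot be estimated from the document. The firm figures are the 12-point ceiling and the 0.53 step per item that makes up the 1.6-point target. The 26% and 74% in the working show how sensitive the test is to small assumed shifts and do not predict error rates. The conclusion rests on one inference, that the three items score absence of contact, which follows from the stated direction of the scale. It does not extend to the binary definition of delirium, and it gives no reason to change the sample size.

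**What to change.** Keep the arrival PAED score as the primary outcome, with its sample size.

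- **Measurements:** have the blinded PACU assessor record awake or asleep (or a level of arousal) at each PAED score.
- **Statistical analysis:** report the share asleep at arrival by arm, and prespecify two supporting analyses of the primary comparison: (a) the restlessness plus consolability sub-score (0–8) at the first assessment, and (b) the first PAED score taken once the child is awake.
- **Interpretation:** conclude a reduction in delirium only if both supporting analyses agree in direction with the primary result. Otherwise report a lower PAED score whose source, arousal or delirium, is unresolved. Agreement in direction is a low bar, so give both estimates with confidence intervals.

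The cost is one tick-box for an assessor already present and two extra analyses. Wakefulness will be unavailable for children already enrolled unless it was noted, whereas the sub-score is available wherever item scores were recorded. Neither supporting analysis is free of arousal: a sleeping child cannot be restless, and the first-awake score varies in timing. This is why both are needed, and why neither should replace the primary.

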### Sample size

The primary outcome is the initial PAED score. In our pilot study, the mean difference of the PAED score between the stranger group and the maternal group was 1.6 with a standard deviation (SD) of 2.19. To attain an alpha value of 0.05 and a test power of 0.8, 30 patients are needed in each group using the following formula [16]. We plan to enroll a total of 66 patients to allow for a 10% dropout rate:$$ n\kern0.5em =\kern0.5em \frac{2{\left({z}_{a/2}+{z}_{\beta}\right)}^2\kern0.5em \cdotp \kern0.5em {\sigma}^2}{{\left({\mu}_c-{\mu}_t\right)}^2} $$

To compensate for the possibility of an over-estimated effect size of the pilot study, we will perform an interim analysis at 50% enrollment. If the sample size has significantly lower power than our expectation, we will recruit more patients. Otherwise, we will continue the study according to our initial sample size calculation.

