### Randomization and blinding

After recruitment, the participants will be randomized to the maternal group or the stranger group with a 1:1 ratio (Fig. 2) using a computerized online tool (www. Randomization.com). A random sequence will be managed and kept within sealed, opaque envelopes by an assistant who is not involved in this study. When a patient is enrolled in the study, an anesthesia nurse will open a sealed envelope and prepare the mother’s or a stranger’s recorded voice file using a voice recorder according to the group allocation. The voice recorder will be delivered to the operating room after the patient arrives and will be connected to noise-cancelling headphones before surgical draping.

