### Statistical analysis

An intention-to-treat analysis will be performed and missing data will be input with the last-observation-carried-forward method. Continuous variables will be presented as the mean and the SD or the median and the interquartile range (IQR) according to the normality assumption using the Kolmogorov-Smirnov test. Categorical variables will be presented as numbers of patients and proportions.

The primary outcome (the initial PAED score) will be compared with an independent *t* test or a Mann-Whitney *U* test. For secondary outcomes, continuous variables will be compared with an independent *t* test or the Mann-Whitney *U* test and categorical variables will be compared with Pearson’s chi-squared test or Fisher’s exact test. All tests are two-sided and *P* < 0.05 is considered statistically significant. A statistician ([name]) who is not involved in the data collection will conduct all statistical analyses with SPSS software (version 21.0; SPSS Inc., IBM, Chicago, IL, USA).

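### The 50% interim can enlarge the trial on the strength of interim results, but the final test is an ordinary pooled test at an unadjusted 0.05, so the stated 5% type I error is not guaranteed

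*Protocol article*

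**What the plan says.** The Sample size section of the protocol article rests on a pilot in which "the mean difference of the PAED score between the stranger group and the maternal group was 1.6 with a standard deviation (SD) of 2.19". It concludes: "To attain an alpha value of 0.05 and a test power of 0.8, 30 patients are needed in each group". Enrolment is then raised: "We plan to enroll a total of 66 patients to allow for a 10% dropout rate".

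The same section adds an adaptation: "To compensate for the possibility of an over-estimated effect size of the pilot study, we will perform an interim analysis at 50% enrollment". The decision rule is "If the sample size has significantly lower power than our expectation, we will recruit more patients", and the alternative is "Otherwise, we will continue the study according to our initial sample size calculation". So the sample can only stay the same or grow, and no early stop for efficacy is mentioned. The text does not say which interim quantity feeds the power assessment, or whether the look is blinded.

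The Statistical analysis section assigns the initial PAED score to an independent t test or a Mann-Whitney U test and sets one level for everything: "All tests are two-sided and *P* < 0.05 is considered statistically significant". It does not mention the interim.

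**The concern.** An interim meant to detect an over-estimated effect would normally look at the between-arm difference, here with about 16 or 17 children per arm. If the final size is chosen from that difference and all patients are then pooled with equal weight, the usual test statistic no longer has its usual null distribution. The direction is unfavourable: a rule that adds patients when the interim effect is small enlarges the trial where the pooled test then rejects too often.

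At stake is whether the single primary comparison can be reported at the 5% level for which the trial was sized. Someone who disputes a positive result obtained after an enlargement would have a ready objection.

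**Working it through.** **1. The plan's own figure.** Inputs from the Sample size section: difference 1.6, SD 2.19, two-sided alpha 0.05, power 0.80.

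n = 2 × (1.960 + 0.842)² × 2.19² / 1.6² = 29.4, rounded up to 30 per arm. Then 30 × 1.1 = 33 per arm, or 66 in total. The stated figures are reproduced. A one-sided calculation would give 24 per arm, so the design is two-sided.

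**2. Why the pooled test inflates.** Let stage 1 be half of the planned information and let the final size be r times the plan. The pooled statistic is Z = (√0.5 · z₁ + √(r − 0.5) · z₂) / √r, where z₁ and z₂ are the stage-wise statistics. Suppose the interim shows no effect at all (z₁ = 0). The null probability of rejecting at the end is then:
- at the planned size (r = 1): |z₂| must exceed 1.960 / √0.5 = 2.772, probability 0.0056;
- at double the size (r = 2): |z₂| must exceed 1.960 × √2 / √1.5 = 2.263, probability 0.0236.

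Enlarging after a flat interim therefore raises the chance of a false positive.

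**3. Overall type I error.** Simulation under the null with 2,000,000 trials per setting: interim at 16 per arm, 33 per arm planned, n re-estimated to 80% power from the observed effect and SD, increases only, final pooled t test at two-sided 0.05. The maximum size is an assumption. The absolute-effect rule ignores which arm is ahead. The signed rule does not let an unfavourable difference count as a large effect. The last column is the worst possible increase-only rule, obtained by numerical integration with known variance and the interim at half the information.

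| Maximum, multiple of plan (per arm) | Absolute-effect rule | Signed rule | Worst case |
|---|---|---|---|
| 1.5 (about 50) | 5.6% | 5.3% | 5.8% |
| 2 (66) | 6.0% | 5.5% | 6.2% |
| 3 (99) | 6.4% | 5.7% | 6.6% |
| 4 (132) | 6.6% | 5.8% | 6.8% |
| 10 (330) | 7.0% | 6.0% | 7.3% |
| practically none | – | – | 7.5% |

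Without adaptation the same simulation gives 5.0%. Using 15 of 30 per arm instead of 16 of 33 gives the same picture. Under the null the 80% trigger is met in about 94–97% of trials. A stricter trigger does not remove the excess: enlarging only when power falls below 50% gives 6.2% for the absolute-effect rule at twice the plan (15 of 30 per arm).

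**4. How often the trial would grow if the planned effect is true.** The interim standard error with 16 per arm is 2.19 × √(2/16) = 0.774. The final standard error with 33 per arm is 2.19 × √(2/33) = 0.539. Projected power falls below p when the interim difference is below (1.960 + z_p) × 0.539. With a true difference of 1.6:

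| Trigger: power below | Interim difference below | Probability |
|---|---|---|
| 80% | 1.51 | 45% |
| 70% | 1.34 | 37% |
| 60% | 1.19 | 30% |
| 50% | 1.06 | 24% |

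**5. Alternatives that hold the level.** An inverse-normal combination with weights fixed at the planned split gives 5.0% at maxima of 2, 3 and 4 times the plan. Re-estimation from the SD alone, with the effect held at 1.6 and the ordinary t test kept, gives about 5.0–5.1%.

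**The case against.** The article never says that the interim compares the arms. Allocation is concealed from the investigators, and a statistician outside data collection does the analyses. If effect size means the standardised difference, an SD set too low in the pilot would also have over-stated it, and a pooled-SD review would address that with almost no inflation. This stands as a limit: the between-arm look is an inference. It remains the more natural reading, because an SD-only review cannot show that a mean difference of 1.6 was too large.

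The article is also a condensed account, and a separate analysis plan may exist. The missing trigger, formula and maximum are details commonly placed there, so their absence is not raised as a defect. What remains is the pairing that the article does state: an adaptation, followed by named ordinary tests at an unadjusted 0.05.

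The excess is also small. A tenfold enlargement is implausible at a single centre. The hypothesis is directional, which makes the signed rule at least as plausible as the absolute one, and some promising-zone rules do not inflate at all. All of this stands and lowers the weight of the point without removing it.

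A reader might go further in three ways that the documents do not support:
- That the error rate has no bound. It has one, because the article allows only an increase or no change.
- That the error is 8.3%, the figure for two looks each tested at 0.05. No efficacy test or efficacy stop at the interim is stated.
- That the trigger is a coin toss under the planned effect. The 45% counts any projected power below 80%, whereas the article requires a significant shortfall, and stricter definitions bring the figure down to 24%.

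**Conclusion.** The point holds in a limited form. On the natural between-arm reading, the stated adaptation and the stated final test do not together guarantee 5%. With an 80% power trigger and growth to no more than 50–66 per arm, the error is about 5.3–6.0%, an excess of 0.3–1.0 percentage points. It reaches 7.0% only with very large maxima and is at most about 7.5% for any increase-only rule without an efficacy stop. These figures assume normal data, a t test and maxima that the article does not give.

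It would be too strong to say that no positive result could be claimed at 5%: if the unwritten rule turned out to be SD-only or a suitable promising-zone rule, the level would hold. This should be fixed, but it does not invalidate the design.

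**What to change.** Settle the rule before any interim data are seen. Recruitment is already under way, and a rule written after the look would itself appear data-driven.

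**Option 1, which keeps the stated aim.** Let the independent statistician re-estimate n from the interim effect, with a written trigger, a fixed maximum and an explicit statement that there is no efficacy stop. Replace the final primary test with an inverse-normal combination of the stage-wise p-values, with weights fixed at the planned information split. The cost is protocol wording, a few lines of code and about 1 power point at most. In simulation with a true difference of 1.6, power goes from 0.832 to 0.829 with no increase, from 0.931 to 0.920 with a maximum of 50 per arm, and from 0.956 to 0.949 with a maximum of 66 per arm.

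**Option 2, which is simpler.** Re-estimate n from the blinded pooled SD only, hold the difference at 1.6 and keep the ordinary final test. The cost is that the interim no longer corrects an over-estimated mean difference, so the stated purpose in the Sample size section would have to be reworded.

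Under either option, amend the Statistical analysis section to name the final primary test that applies after the interim.
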